**Fig. 1 Fig1:**
[figure not shown]
Flowchart of participants in the Covered stents versus Bare-metal stents in chronic atherosclerotic Gastrointestinal Ischemia (CoBaGI) trial according to Consolidated Standards of Reporting Trials (CONSORT) [25]

### Follow-up

After the endovascular procedure, the patients are followed up at 6, 12 and 24 months with CTA to assess stent patency and with a visit to the outpatient clinic to assess symptoms and bodyweight. The patients also receive questionnaires to assess quality of life and cost-effectiveness before stent placement and 6, 12 and 24 months after stent placement.

### Outcome

The primary endpoint is the primary patency rate 24 months after stent placement based on intention-to-treat analyses.

The secondary endpoints are (definitions are shown in Table 2):
Primary patency rates at 6 and 12 monthsSecondary patency rates at 6, 12 and 24 monthsFreedom from restenosis at 6, 12 and 24 monthsFreedom from symptom recurrence at 6, 12 and 24 monthsFreedom from re-intervention at 6, 12 and 24 monthsQuality of life at 6, 12 and 24 monthsCost-effectiveness at 6, 12 and 24 months

**Table 2 Tab2:** Definitions

	Definition
Restenosis	> 50% intra-stent stenosis regardless whether the patient had clinical symptoms
Symptom recurrence	Occurrence of presenting symptoms regardless of stent patency
Re-intervention	Intervention due to symptom occurrence in the presence of > 50% intra-stent stenosis, either a reimplantation of stent, or a surgical procedure

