Currently, balloon-expendable bare-metal stents (BMS) are standard care for mesenteric endovascular revascularization [1, 20]. Retrospective data, however, showed significantly higher primary patency rates of balloon-expendable covered stents (CS) at 3 years for mesenteric artery stenosis [21]. Furthermore, patients treated with CS had less restenosis, symptom recurrence and re-intervention than patients treated with BMS [21]. The Covered versus Balloon Expandable Stent Trial (COBEST) showed significantly higher patency rates of CS than BMS for aortoiliac arterial disease 18, 24, 48 and 60 months after stent placement [22, 23]. Possibly, the membrane that covers the vascular atherosclerotic lesion functions as a physical barrier for intimal hyperplasia and is, therefore, associated with less restenosis in contrast with BMS. The performance of CS for mesenteric artery stenosis is promising, but prospective confirmation is lacking. The CoBaGI trial is a multicenter, randomized controlled, patient- and investigator-blinded clinical trial designed to compare patency rates of the CS versus standard care therapy with BMS in patients with CMI based on atherosclerosis.

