### Sample size

The sample size calculation for this randomized controlled, superiority trial is based on the retrospective data of Oderich et al. [21]. Assuming that CS improves the patency rate of BMS after 24 months from 63% to 95%, and accounting for a 20% dropout rate, 42 participants are required per arm to achieve 80% power with a two-sided alpha of 0.05. The sample size calculation is performed using the Comparison of Independent Proportions Test (SAS Power and Sample size, SAS Institute Inc., Cary, NC, USA).

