Of note is the inclusion criterion that the length of the stenosis cannot exceed 24 mm because all stenoses needing stent extension had to be excluded in the CoBaGI trial since a CS will obstruct blood flow when a side-branch is over-stented in contrast to a BMS. The longest available Palmaz Blue BMS during the inclusion of the CoBaGI trial had a length of 24 mm and the longest CS had a length of 59 mm.

A pivotal inclusion criterion for the CoBaGI trial is a consensus diagnosis of CMI based on atherosclerotic mesenteric artery stenosis which is established in a multidisciplinary meeting joined by gastroenterologists, interventional radiologists and vascular surgeons. Medisch Spectrum Twente and Erasmus MC University Medical Center are specialized CMI referral centers. All patients eligible for the CoBaGI trial, therefore, will be discussed during a CMI multidisciplinary meeting in one of these two centers. If functional assessment of mucosal ischemia is required to reach a consensus diagnosis, especially in case of single-vessel disease, the patient is referred to Erasmus MC University Medical Center (VLS) [10, 11] or Medisch Spectrum Twente (24-h tonometry) [3, 8, 9].

After endovascular revascularization for CMI, antiplatelet therapy is recommended and dual antiplatelet therapy might be considered for 3–12 months [1]. Exact dose and duration schedules are lacking for mesenteric revascularization. All stented patients in the CoBaGI trial, regardless of allocation, will receive aspirin and clopidogrel for 12 months after stenting followed by aspirin lifelong.

The true incidence of atherosclerotic CMI is unknown. It is expected that in the upcoming years the incidence of atherosclerotic CMI will increase, mainly because of the aging population and the increasing prevalence of cardiovascular disease. The predicted increase in the prevalence of atherosclerotic CMI, the significant patient burden in terms of pain and loss of quality of life, and, in particular, the risk of an acute ischemic event with an exceedingly high mortality risk, underscore the importance of the CoBaGI trial. The CoBaGI trial aimed to improve the patient outcome in terms of pain relief, improvement of quality of life and prevention of acute ischemic events. The fact that the CoBaGI trial is carried out within the framework of the DMIS with patients being recruited from multiple academic and community hospitals should facilitate the generalizability of the study outcomes.

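### Restenosis and re-intervention count only narrowing inside the stent, so a re-treated stenosis at the stent edge is scored as free from both, with a bias of unknown size and direction

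*Protocol article*

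**What the plan says.** All references are to the protocol article.

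- **Restenosis** (Outcome, Table 2): "> 50% intra-stent stenosis regardless whether the patient had clinical symptoms".
- **Re-intervention** (Table 2): "Intervention due to symptom occurrence in the presence of > 50% intra-stent stenosis, either a reimplantation of stent, or a surgical procedure".
- **Symptom recurrence** (Table 2): "Occurrence of presenting symptoms regardless of stent patency".
- **Primary endpoint** (Outcome): "The primary endpoint is the primary patency rate 24 months after stent placement based on intention-to-treat analyses". Definitions are announced for the secondary endpoints ("The secondary endpoints are (definitions are shown in Table 2"), but the table has no row for primary or secondary patency.
- **Mechanism** (Background): the article suggests, prefacing it with 'possibly', that "the membrane that covers the vascular atherosclerotic lesion functions as a physical barrier for intimal hyperplasia". It says nothing about the stent edges.
- **Stent and lesion length** (Eligibility criteria; Discussion): lesions must be shorter than 25 mm. The longest BMS available was 24 mm and the longest CS 59 mm.
- **Imaging** (Follow-up): CTA at 6, 12 and 24 months.

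**The concern.** The word 'intra-stent' appears in both anatomical definitions and so decides what counts as failure. Take a patient whose artery closes down just proximal or distal to the stent, whose symptoms return, and who has a second stent placed. There is no stenosis inside the first stent, so neither the restenosis rule nor the re-intervention rule is met. Clinically the treated artery has failed and been treated again, yet two listed secondary endpoints record success at 6, 12 and 24 months.

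The restriction matters more in a comparison of two stents than in a single series. If edge lesions are not equally common in the two arms, leaving them out shifts the CS versus BMS contrast. If primary patency is read with the same threshold, that shift reaches the primary endpoint as well.

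**Working it through.** **1. Which endpoints register an edge-only lesion, reading Table 2 literally**

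| Patient | Restenosis | Re-intervention | Symptom recurrence |
|---|---|---|---|
| In-stent > 50%, symptoms, second stent | counted | counted | counted |
| Edge only > 50%, symptoms, second stent | not counted | not counted | counted |
| Edge only > 50%, no symptoms | not counted | not counted | not counted |

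Primary patency cannot be placed in this table, because the article gives no rule for it.

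**2. Effect on the difference between arms**

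Inputs from the document (Sample size): 24-month patency of 63% for BMS and 95% for CS, a difference of 32 points. Two assumptions are needed: that these are in-stent rates, and that a share *e* of otherwise patent stents has an edge-only stenosis. The document gives no value of *e* for either arm.

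Patency counting edges = in-stent patency × (1 − *e*).

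| Assumed *e*, CS | Assumed *e*, BMS | CS | BMS | Difference |
|---|---|---|---|---|
| 0 | 0 | 0.950 | 0.630 | 32.0 points |
| 5% | 3% | 0.95 × 0.95 = 0.9025 | 0.63 × 0.97 = 0.6111 | 29.1 |
| 10% | 3% | 0.95 × 0.90 = 0.855 | 0.6111 | 24.4 |
| 15% | 3% | 0.95 × 0.85 = 0.8075 | 0.6111 | 19.6 |
| 10% | 10% | 0.855 | 0.63 × 0.90 = 0.567 | 28.8 |
| 3% | 10% | 0.95 × 0.97 = 0.9215 | 0.567 | 35.5 |

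In general the difference is 0.32 − 0.95 *e*(CS) + 0.63 *e*(BMS). It stays at 32 points when *e*(BMS) / *e*(CS) = 0.95 / 0.63 = 1.51. Above that ratio the in-stent definition understates the CS advantage; below it, it overstates it.

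The equal-risk row needs care. The absolute gap shrinks to 28.8 points because more CS stents are patent and so exposed to reclassification, but the ratio is unchanged: 0.855 / 0.567 = 0.95 / 0.63 = 1.51. If instead the same number of percentage points is taken off each arm, the gap stays at 32.

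**3. Sensitivity of the trial's power**

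The plan has 42 per arm and 20% dropout: 42 × 0.8 = 33.6 evaluable. A pooled two-sample z-test of 63% against 95% then has 91.5% power. (The stated 80% does not reproduce 42: the same test needs 25 evaluable, or 32 after dropout. That is a separate matter.) Now subtract edge failures as absolute points, assuming patency follows the in-stent threshold:

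| Edge failures counted in | 2 points | 5 points | 10 points |
|---|---|---|---|
| CS only | 86.0% | 75.4% | 53.9% |
| both arms equally | 89.4% | 86.6% | 82.5% |
| BMS only | 93.8% | 96.4% | 98.7% |

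With CS-only failures, power drops below 80% from about 3.8 points, which is 0.038 × 33.6 = 1.3 patients. One or two reclassified patients in one arm are therefore enough to matter at this sample size.

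**The case against.** A reader might infer something stronger: that an edge stenosis is scored as a patent success on the primary endpoint, and that this favours the covered stent. The documents support neither step.

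- **Patency.** The article never defines it. It condenses a fuller protocol (version 5) that is not shown, and the rule for reading patency, including the segment assessed, may sit there. Equating patency with absence of Table 2 restenosis is a natural guess, but only a guess.
- **Direction.** No edge rate is given for either arm. The barrier mechanism is offered tentatively and concerns the covered lesion only. It could point towards CS, since the endpoint looks only where the membrane acts. The stent lengths could point the other way: a BMS of at most 24 mm on a lesion just under 25 mm has little or no margin, so its ends may lie nearer diseased wall. Scenarios that always give CS more edge failure would assume the answer.

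Three further objections have weight. The stated target is *stent* patency, and an in-stent criterion fits that target and keeps comparability with earlier series. Symptomatic edge lesions are not lost altogether, because they count as symptom recurrence, and the cost questionnaire records healthcare use. And with 71 of 84 patients included by September 2018 (Trial status), replacing the primary endpoint would mean redefining it with follow-up under way.

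These objections rule out the strong reading and a change of primary endpoint. They do not rescue the two secondary definitions. A second stent in the treated artery for returning symptoms is a re-intervention in any ordinary sense, and Table 2 excludes it by a stated rule, not by omitted detail.

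**Conclusion.** The point holds for freedom from restenosis and freedom from re-intervention: as written, both miss a lesion at the stent edge, and the second misses the repeat procedure done for it. For primary patency it holds only on the condition that patency uses the same threshold. A silent edge lesion is recorded under no listed endpoint.

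The size and direction of any bias between the arms cannot be determined from the article. The span of roughly 20 to 35 points around the planned 32 rests wholly on assumed edge risks of 3% to 15% and on reading 63% and 95% as in-stent rates. It shows that the gap could move either way, not that it does. This is a correctable weakness in secondary definitions and a reason for a supporting analysis. It does not invalidate the primary comparison.

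**What to change.** 1. In Table 2, count as re-intervention any repeat stent or surgical procedure on the treated vessel segment for recurrent symptoms, whether the stenosis is inside the stent or at its edge.
2. Keep the in-stent definition of restenosis, for comparability.
3. Add a prespecified supporting analysis of patency and restenosis that counts > 50% stenosis or occlusion within the stent or within a fixed margin of either edge. The documents give no margin, so its width must be chosen and written down before the arms are compared. Report it beside the in-stent result, by arm.
4. State in the article's definitions whether primary patency uses the in-stent threshold.

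**Cost.** An edit to Table 2 and to the CTA reading form, plus a modest amount of extra reading of CTAs already scheduled at 6, 12 and 24 months. Scans already read would need a second look; the article does not say how they are stored, so this should be confirmed at each center. Reported freedom from re-intervention may be slightly lower, as may patency and freedom from restenosis in the supporting analysis. The primary endpoint is not replaced.

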**Methods/design:**

The CoBaGI trial is a randomized controlled, parallel-group, patient- and investigator-blinded, superiority, multicenter trial conducted in six centers of the Dutch Mesenteric Ischemia Study group (DMIS). Eighty-four patients with a consensus diagnosis of atherosclerotic CMI are 1:1 randomized to either a balloon-expandable BMS (Palmaz Blue with rapid-exchange delivery system, Cordis Corporation, Bridgewater, NJ, USA) or a balloon-expandable CS (Advanta V12 over-the-wire, Atrium Maquet Getinge Group, Hudson, NH, USA). The primary endpoint is the primary stent-patency rate at 24 months assessed with CT angiography. Secondary endpoints are primary stent patency at 6 and 12 months and secondary patency rates, freedom from restenosis, freedom from symptom recurrence, freedom from re-intervention, quality of life according the EQ-5D-5 L and SF-36 and cost-effectiveness at 6, 12 and 24 months.

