### Blinding

The patient, investigator and the treating physician at the outpatient clinic are blinded for the treatment allocation (BMS or CS). For the duration of the trial the allocated stent will not be disclosed unless there is a medical need (i.e., restenosis, stent fracture).

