### Statistical methods

Descriptive analyses will be provided regarding patient characteristics before randomization. Because this is a randomized controlled trial, statistical tests to detect differences in these baseline characteristics between both intervention arms will not be performed. The following patient characteristics before randomization will be provided: age, gender, Body Mass Index (BMI), smoking status, comorbidity with hypertension, dyslipidemia, diabetes and cardiovascular disease. Furthermore presenting symptoms will be described as abdominal pain, postprandial pain, exercise-related pain, nausea, diarrhea, weight loss and symptom duration. Patient characteristics will be described as numbers and percentages for dichotomous variables, or as means and standard deviations for continuous variables with normal distribution or medians and interquartile ranges (IQRs) for continuous variables if not normally distributed.

The primary analysis will be performed according the intention-to-treat principle. A per-protocol analysis will also be performed for the primary outcome of stent patency for those patients who were treated according to the treatment protocol.

The primary endpoint of stent patency will be analyzed with a “two-sample z-test” for comparison of two proportions. Furthermore, a predictive model for time-to-event will be obtained by proportional hazards regression and Kaplan-Meier analysis to compare patency rates of CS versus BMS. All other continuous outcome measures will be reported as difference in mean improvement between the CS versus the BMS group. Change in quality of life assessed by the validated questionnaires EQ-5D-5 L [26, 27] and SF-36 [28, 29] will be compared between the CS and BMS groups. Furthermore, the costs of both groups will be compared. All costs will be estimated based on actual input in terms of resource use, personnel and indirect costs from loss of productivity assessed by the cost-effectiveness questionnaire.

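### The re-intervention definition in Table 2 leaves out repair by balloon, thrombolysis or thrombectomy alone, and the table does not define primary or secondary patency

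*Protocol article*

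**What the plan says.** In the Outcome section, the primary endpoint is given in one sentence: "The primary endpoint is the primary patency rate 24 months after stent placement based on intention-to-treat analyses". The abstract adds only the imaging method: "The primary endpoint is the primary stent-patency rate at 24 months assessed with CT angiography".

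The secondary list opens with "The secondary endpoints are (definitions are shown in Table 2" and then names primary patency at 6 and 12 months, secondary patency, and freedom from restenosis, from symptom recurrence and from re-intervention. Table 2 has three rows: restenosis, symptom recurrence and re-intervention.

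- Restenosis: "> 50% intra-stent stenosis regardless whether the patient had clinical symptoms".
- Re-intervention: "Intervention due to symptom occurrence in the presence of > 50% intra-stent stenosis, either a reimplantation of stent, or a surgical procedure".

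The Follow-up section says that "the patients are followed up at 6, 12 and 24 months with CTA to assess stent patency". The Blinding section says that "the allocated stent will not be disclosed unless there is a medical need (i.e., restenosis, stent fracture". The Statistical methods section says: "The primary endpoint of stent patency will be analyzed with a “two-sample z-test” for comparison of two proportions". It adds Kaplan-Meier and proportional hazards analyses of patency.

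**The concern.** Table 2 sets three conditions for a re-intervention, and all must hold: symptoms, more than 50% stenosis in the stent, and a procedure that is either a new stent or surgery. Balloon dilatation, thrombolysis and thrombectomy are other ways to reopen a stent, and none of them meets the third condition. A patient whose symptoms return, whose stent is narrowed by more than 50% and who is treated by balloon alone has plainly had a repeat procedure, yet is reported as free from re-intervention.

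The second gap touches the primary endpoint. Primary and secondary patency normally differ in how they treat repaired stents, but the table that is cited for the definitions mentions neither. A reader of the article cannot tell whether a restenosis or repair before month 24 ends primary patency.

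At stake are the meaning of a named secondary endpoint and, if the full protocol does not settle the matter, the scoring rule for the primary one.

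**Working it through.** **1. Re-intervention, read from the text.** Three cases set against the Table 2 row:

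| Case | Symptoms | >50% in-stent stenosis | New stent or surgery | Counted? |
|---|---|---|---|---|
| New stent for symptomatic restenosis | yes | yes | yes | yes |
| Balloon, lysis or thrombectomy alone for symptomatic restenosis | yes | yes | no | no |
| Any procedure for symptom-free restenosis | no | yes | either | no |

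The second row is the fault, and it needs no assumption. The third row is a stated choice (see the objection).

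**2. Direction.** The Sample size section assumes patency of 63% (BMS) and 95% (CS), so failure is 1 − 0.63 = 37% and 1 − 0.95 = 5%. With 42 per arm and 20% dropout, 42 × 0.8 = 33.6 are evaluable. Expected failures are 0.37 × 33.6 = 12.4 (BMS) and 0.05 × 33.6 = 1.7 (CS). If true re-intervention rates are r_B and r_C and a share s goes uncounted in both arms, the observed difference is (1 − s)(r_B − r_C). The absolute difference shrinks by the share s; the ratio does not change, but it rests on fewer events. The documents give neither r_B, r_C nor s, so the loss for this endpoint cannot be sized. An equal s is itself an assumption: allocation may be disclosed at restenosis, so the type of repair may be chosen by someone who knows the arm.

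**3. Primary patency, illustration only.** First, the plan's own figure. The pooled z-test formula for 63% vs 95%, two-sided alpha 0.05 and 80% power gives 25 per arm, and 25 / 0.8 = 31.25, so 32 with dropout. The stated 42 is larger. That difference is on the safe side and does not bear on this point.

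Power with n per arm is Φ[(d√n − 1.96·√(2p̄(1 − p̄))) / √(p_B(1 − p_B) + p_C(1 − p_C))], where d = p_C − p_B and p̄ is the mean of the two rates. If a share f of failures in each arm is rescored as patent, p_B = 0.63 + 0.37f and p_C = 0.95 + 0.05f. With n = 33.6 (√n = 5.797):

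| f (assumed) | BMS | CS | Difference | Power |
|---|---|---|---|---|
| 0 | 63.0% | 95.0% | 32.0 points | Φ(1.37) = 91% |
| 1/5 | 70.4% | 96.0% | 25.6 points | Φ(0.90) = 82% |
| 1/3 | 75.3% | 96.7% | 21.3 points | Φ(0.59) = 72% |

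For f = 0: (0.32 × 5.797 − 1.96 × 0.576) / 0.530 = 1.37.

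**The case against.** A reader might infer that the article literally scores a stent re-dilated at month 9 and open at month 24 as primarily patent. It does not. No sentence says so, and nothing ties primary patency to the re-intervention row. The context points the other way. Secondary patency at 24 months is listed as a separate endpoint, which would add little if repair did not end primary patency. Patency is also analysed as time to event, where a later reopening would not normally undo a loss. CTAs at 6 and 12 months can record a failure before the last scan. The full protocol, which is not shown, may hold the definition. All of this stands. What remains is narrower: the article names Table 2 as the place for its definitions and the table lacks them, so the reading is not excluded.

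A reader might also call the symptom requirement an error. Symptom-driven re-intervention is a defensible endpoint. Symptom-free failures are still counted as restenosis, which is defined regardless of symptoms and reported at 6, 12 and 24 months. The same holds for a balloon-treated stent if the stenosis was recorded. So these patients do not vanish from the trial's results; they are missing from the re-intervention endpoint.

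On size, the share of failures repaired without a new stent or surgery is unknown. Rescoring BMS failures alone would give a larger loss of power, but the same definition applies to both arms. With one fifth rescored in both, power stays above the stated 80%. The expected direction is also toward no difference, which threatens power more than it risks a false claim for covered stents.

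None of this rescues the list of procedure types. A symptomatic restenosis repaired by balloon alone is left out by what the table says, whatever the full protocol says about patency.

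**Conclusion.** The point holds in two parts of unequal strength.

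The re-intervention rule is wrong as stated: it leaves out symptomatic restenosis reopened by balloon, thrombolysis or thrombectomy alone. This follows from the wording. That the undercount falls mostly in the BMS arm and narrows the absolute difference rests on the planning rates (37% vs 5% failures) and on a similar uncounted share in the two arms.

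The absence of patency definitions from Table 2 is a gap, and scoring a repaired stent as primarily patent is a possible reading, not the stated rule. The fall in power from about 91% to about 82% or 72% shows what that reading could cost at an assumed share of one fifth or one third in both arms. It is not an estimate of what will happen.

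Severity: should be fixed.

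**What to change.** Reword Table 2 as follows.

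- **Re-intervention:** any repeat endovascular procedure (balloon, stent, lysis, thrombectomy) or open procedure on the study-stented vessel after the index procedure. Report symptom-driven re-intervention as a sub-category, so that the present clinical meaning is kept.
- **Primary patency at 24 months:** no in-stent stenosis above 50% and no occlusion on any CTA up to and including 24 months, and no re-intervention as defined above.
- **Secondary patency:** an open stent regardless of re-intervention.

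If the full protocol already defines patency, check that it agrees and carry its wording into the table.

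This concerns only how events are counted and does not touch how patients are treated. The CTAs are already scheduled. The cost lies in the procedure data: the Interventions section describes case record forms for the index procedure, and the article does not say how later ones are captured, so some may have to be retrieved from hospital records. The change should be dated and made before the 24-month data are analysed. With 71 of 84 patients included in September 2018 and two years of follow-up, there was time for that when the article was written.
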